### Outcomes

2.3

As a pilot and first study of corticosteroid in adults with pneumonia-related pleural effusions, we aim to capture a wide range of clinically relevant endpoints which have been used in clinical trials of pneumonia and/or pleural infection, and are considered by clinicians as important. These include:

1.The time to clinical stability defined as the time in hours for all of the following parameters to have been maintained for at least 12 hours: temperature ≤37.4°, heart rate ≤100 bpm, respiratory rate ≤20/min, oxygen saturations ≥95% on room air (unless on home oxygen), systolic blood pressure ≥90 mmHg and tolerating oral intake or discharge home (determined by the treating physician)^[28]^;2.The time in hours for each of the above parameters to have been maintained for least 12 hours;3.Change in leukocyte count and C-reactive protein (CRP) over time (Day 0, 1, 3, 14 ± 2 days, 30 ± 2 days);4.Proportion of participants with a normal leukocyte count and CRP at Day 14 ± 2 and Day 30 ± 2;5.Improvement in pleural effusion including size of pleural opacity as percentage of hemithorax (as used in our prior studies)^[29]^ over the first 14 ± 2 days and at Day 30 ± 2 compared with baseline; and proportion of participants whose effusion has resolved at day 14 ± 2 days and day 30 ± 2;6.Proportion of participants requiring an invasive pleural procedure including therapeutic aspirate (volume >200 mL) or chest drain insertion at <48 hours and >48 hours post-commencement of treatment. If intercostal catheter is inserted, the following will be recorded:a.Duration of chest tube drainage;b.Volume of fluid drained daily;c.Proportion treated with intrapleural fibrinolytic therapy; andd.Proportion requiring additional drainage procedures including additional chest drain insertion and therapeutic thoracentesis.7.Proportion of patients referred for thoracic surgery;8.Duration of antibiotic therapy (intravenous and oral);9.Length of hospital stay from commencement of treatment to discharge or death;10.Quality of life measurements including Short form-36 (SF-36) questionnaire^[30]^ and actigraphy (see Section 2.7 for details);11.Adverse events including but not limited to hyperglycemia, insulin use, need for intensive care, nosocomial infection, gastrointestinal bleeding and re-admission to hospital of any cause; and12.Overall survival.

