### Randomization and blinding

2.5

Participants will be randomly assigned (2:1) to receive intravenous dexamethasone or placebo. The National Health and Medical Research Council Clinical Trials Centre, Sydney, Australia provides the randomization setup via their automated telephone-based interactive voice response services. Randomization is minimized for:

(i)A score of <2 versus ≥2 using the predictive score of Chalmers et al^[6]^ for the development of complicated pleural effusion/empyema secondary to pneumonia (one point each for: serum albumin <30 g/L, CRP >100 mg/L, platelet count >400 × 10^9^/L, serum sodium <130 mmol/L, intravenous drug use, and chronic alcohol excess. One point will be deducted for the presence of COPD);(ii)Known history of diabetes mellitus (vs not); and(iii)Size of the effusion on chest radiograph (a grading of ≤2 vs >2 and/or having an intercostal catheter in place).^[31]^

The research team, treating physician, nursing staff, and participant will be blinded to the treatment arm. Only pharmacy staff will receive unblinded randomization information in order to prepare the study drug or placebo. In the event that unblinding is required, a designated member of the lead research team will be contacted and will follow the unblinding SOP.

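### Drain outcomes 6a–d exist only in participants who receive a catheter, so comparing the arms within that subset is not protected by randomization.

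*Protocol article*

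**What the plan says.** All references are to the protocol article.

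- **Outcomes, item 6.** The parent outcome is "Proportion of participants requiring an invasive pleural procedure including therapeutic aspirate (volume >200 mL) or chest drain insertion", timed "at <48 hours and >48 hours post-commencement of treatment". The sub-items follow the words "If intercostal catheter is inserted, the following will be recorded": (a) duration of drainage, (b) daily volume, (c) proportion given intrapleural fibrinolytics, (d) proportion needing further drainage. No value is assigned to participants without a catheter.
- **Outcomes, item 5.** It covers "Improvement in pleural effusion including size of pleural opacity as percentage of hemithorax" and the "proportion of participants whose effusion has resolved at day 14 ± 2 days and day 30 ± 2". It does not mention drainage.
- **Randomization and blinding, factor (iii).** Minimization uses "Size of the effusion on chest radiograph (a grading of ≤2 vs >2 and/or having an intercostal catheter in place". No exclusion criterion removes participants who already have a catheter, so they can be randomized. Treating clinicians are blinded.
- **Statistical methods.** Analysis is by intention to treat, with between-group tests judged at P < .05. No exception is made for outcomes that exist in only part of the sample.
- **Sample size.** 80 participants, 2:1. The results are to inform power calculations and endpoint choice for later trials.

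**The concern.** The trial's hypothesis is that steroids improve outcome by reducing pleural and systemic inflammation. If that is right, fewer dexamethasone participants may need a drain, and those who still do may not resemble the drained placebo participants. Suppose the cases spared are the milder ones. The drained dexamethasone group is then more severe on average, and its drains may stay longer and need fibrinolytics more often, although the drug has done nothing but prevent drains. If the more severe cases were spared, the distortion would run the other way.

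This matters even in a pilot, because the stated use of the results is to choose endpoints and set power for future trials. A duration or fibrinolysis result with a misleading sign would feed directly into that choice.

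A related gap is that nothing says how a participant who enters with a catheter counts in item 6, or whether that catheter contributes to 6a–d.

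**Working it through.** **Plan's own figure.** The only checkable figure is the arm size: 80 × 2/3 = 53.3 and 80/3 = 26.7, or about 53 and 27. This agrees with the stated 50+ on dexamethasone. No drain rate, drain duration or effect size is given, so every rate below is an assumption.

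**1. Selection in 6a (duration).** Let severity *s* be standard normal, with a participant drained if *s* exceeds the cut that gives drain rate *p*. Let duration have mean 4 and SD 2 days in the whole population, identical in both arms, with correlation ρ to severity. Then

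mean duration among drained = 4 + 2ρ·h(p), where h(p) = φ(z₁₋ₚ)/p.

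h(0.40) = 0.386/0.40 = 0.966; h(0.30) = 0.348/0.30 = 1.159; h(0.25) = 0.318/0.25 = 1.271; h(0.20) = 0.280/0.20 = 1.400.

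The apparent difference (dexamethasone minus placebo) is 2ρ·[h(p₁) − h(p₀)]:

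| Drain rate, placebo vs dexamethasone | ρ = 0.3 | ρ = 0.6 |
|---|---|---|
| 40% vs 40% | 0 | 0 |
| 40% vs 30% | 0.12 d | 0.23 d |
| 40% vs 25% | 0.18 d | 0.37 d |
| 40% vs 20% | 0.26 d | 0.52 d |

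If duration is tied fully to severity (ρ = 1), 40% vs 25% gives 2 × (1.271 − 0.966) = 0.61 days (5.93 vs 6.54). That is an unrealistic ceiling for this pair of rates, and a wider gap in rates would raise it.

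**2. The same data per randomized participant.** Multiply by the drain rate, with zero for the undrained. At 40% vs 25% and ρ = 1: 0.40 × 5.93 = 2.37 and 0.25 × 6.54 = 1.64 drain-days. At ρ = 0.3: 0.40 × 4.58 = 1.83 and 0.25 × 4.76 = 1.19. The sign reverses in both cases, and drain burden is lower on dexamethasone.

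**3. Selection in 6c (fibrinolytics).** Take the same severity scale and the logit of use = −1 + 1.5(*s* − 0.25), with drain rates of 40% vs 25%. Averaged over the drained, use is 51% on placebo and 61% on dexamethasone. Per randomized participant it is 0.40 × 0.51 = 20% and 0.25 × 0.61 = 15%. The sign reverses again.

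**4. Noise.** At 40% vs 25%, the drained number is 27 × 0.40 ≈ 11 on placebo and 53 × 0.25 ≈ 13 on dexamethasone. With SD 2, the standard error of the duration difference is at most 2·√(1/10.8 + 1/13.25) = 0.82 days. Allowing for the smaller spread in a selected group gives about 0.7 (ρ = 0.6) to 0.8 (ρ = 0.3). The artefact is smaller than this.

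**5. Entry catheters in item 6.** Let *b* be the share with a catheter at entry, balanced between arms, with no later event. The risk difference becomes (1 − *b*) times its value in the rest. With *b* = 20% and risks of 30% vs 15%: 0.8 × 30 = 24% vs 0.8 × 15 = 12%. The difference falls from 15 to 12 points, and the risk ratio stays 12/24 = 0.50. With 40% vs 20%, the difference falls from 20 to 16 points, and two-sided power with 27 vs 53 falls from 48% to 39%. With no effect in the rest, the difference is (1 − *b*) × 0 = 0, so none is created.

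**6. Item 5.** If a drain removes an assumed extra 10 points of hemithorax, drain rates of 40% vs 20% move the observed contrast by 10 × (0.20 − 0.40) = −2 points relative to a direct drug effect. It is still the correct contrast between the two randomized strategies.

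**The case against.** The strongest reply on 6a–d is that the protocol says only that these items will be recorded. It does not state a test within the drained subset, and it does not limit the subset to catheters inserted after randomization. Describing drain duration among the drained is ordinary practice, and analysis sets are often left to an analysis plan, which is not shown. The trial is an exploratory pilot in which no outcome is named primary, and the artefact is smaller than the sampling error. Most of this stands, and it limits the consequence. It does not remove the point: 6a–d are listed as endpoints, the restriction to catheter recipients is part of their definition here, and the general rule is an intergroup test at P < .05.

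Three stronger readings are tempting, and the documents do not support them.

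- *Entry catheters bias item 6.* Its events are timed from the start of treatment, so a catheter already in place is naturally not an event. Such a participant can still need a new drain or aspirate. Allocation is random, catheter status enters a minimization factor (merged with effusion grade), and clinicians are blinded. What remains is dilution and an unstated rule. Under *b* = 20% and 30% vs 15%, a risk ratio of (0.20 + 0.12)/(0.20 + 0.24) = 0.73 appears only if entry catheters are counted as events, against that timing.
- *Item 5 is biased because drainage clears fluid.* Under intention to treat it validly compares strategies that include drainage as needed. Scoring drained participants as not resolved answers a different question; it does not correct an error.
- *The protocol commits to comparing only those drained after randomization.* It does not say so. Whether entry catheters feed 6a–d is unclear.

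**Conclusion.** The point holds for 6a–d as a conditional risk. If dexamethasone changes who is drained, a between-arm contrast among drained participants is not a randomized comparison, and it could count against the drug if milder cases are spared. The size cannot be known from the documents. In the scenarios worked here it is about 0.1 to 0.6 days of drain duration, with the upper end needing duration to follow severity completely. It is nil if drain rates are equal. All drain rates, correlations, the duration distribution and the fibrinolysis model are assumptions.

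For item 6, entry catheters shrink the risk difference by their share of the sample and leave the comparison unbiased; the need is for a stated counting rule. Item 5 needs no correction. The change is worth making because these results are meant to guide endpoint choice and power in later trials.

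**What to change.** 1. **6a, 6c, 6d.** Make the between-arm comparison in all randomized participants, with zero or 'no' for the undrained: for example, drain-days to Day 30, proportion given fibrinolytics, and proportion with a further drainage procedure. Report values among drained participants, including daily volume (6b), as description without a between-arm test.
2. **Item 6.** State that only new procedures after treatment starts count as events. Report the result in all participants and also by catheter status at entry. State whether an entry catheter contributes to 6a–d.
3. **Item 5 (optional).** Add resolution without drainage or surgery as a supplementary description, leaving the existing outcome as it is.

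The cost is wording only, since the data are already collected. One trade-off should be acknowledged: drain-days with zeros measure total drain burden, mixing whether a drain was needed with how long it stayed, so they should be read beside the item 6 proportion. The results by entry catheter status will rest on small numbers and should be treated as descriptive.

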## Introduction

1

Community-acquired pneumonia (CAP) is a major global disease.^[1]^ Pneumonia (including influenza) is currently the 8th leading cause of death in the United States^[2]^ and lower respiratory tract infections were the 3rd leading cause of death worldwide in 2015.^[3]^ CAP incurs significant, immediate, healthcare costs as well as economic costs of time lost from work/school and adverse long-term health problems in survivors.^[4,5]^

Parapneumonic effusions complicate 18% to 57% of cases of pneumonia.^[6–8]^ CAP with an effusion is associated with worse outcomes. In one large study of 4700 patients with CAP, those with an effusion at the time of presentation to the emergency department were more likely to require hospitalization and had a length of stay twice that of those without an effusion.^[9]^ Parapneumonic effusions, inadequately treated, may progress to complicated parapneumonic effusions or empyema, both of which have risen in incidence in recent years.^[10,11]^ Conventional management of pleural infection, with antibiotics and chest tube drainage, fails in about 30% of cases. Many of these patients are frail and unsuitable for surgical management and mortality remains high at 8% in hospital and 20% at 3 months.^[11]^ This mortality rate has increased over the past 2 decades, despite advances in antimicrobial therapy.^[12]^

The pathobiology of pleural effusion formation secondary to pneumonia is not fully understood. One hypothesis is that an over-exaggerated inflammatory response triggered by the infection plays a critical role and may be a target for treatment. Steroids have been shown to be successful adjunct therapies in pneumococcal meningitis and Pneumocystis jirovecii pneumonia, likely due to the significant inflammatory component of these conditions.^[13,14]^ The role of systemic corticosteroids as adjunct treatment in pneumonia is a controversial topic with inconsistent results on mortality from large randomized contolled trials (RCTs).^[15]^ The majority of studies have, however, demonstrated benefits of steroids in shortening time to resolution of fever and clinical stability.^[16–22]^ Importantly, all the studies have demonstrated that use of steroids, even in severe pneumonia, was safe with no adverse impact on mortality.^[23,24]^

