### Statistical methods

2.8

Data will be analyzed on an intention-to-treat basis. Intergroup comparison will be conducted using Student *t* test or Mann–Whitney *U* rank sum test (for parametric and non-parametric distributions, respectively). Changes in parameters before and after treatment within the same subject will be analyzed using a paired *t* test or Wilcoxon signed rank test. Correlations will be analyzed using Pearson or Spearman tests. Multivariate analyses may be performed if indicated. *P* < .05 will be considered statistically significant in the data analyses.

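### Length of stay ends at discharge or death alike, so under a t test or Mann–Whitney an early in-hospital death scores as a short stay

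*Protocol article*

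**What the plan says.** Protocol article, Outcomes (2.3), item 9: "Length of hospital stay from commencement of treatment to discharge or death". Discharge and death are one end point.

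Item 1, first in the list, is the "time in hours for all of the following parameters to have been maintained for at least 12 hours". The list of criteria closes with "tolerating oral intake or discharge home (determined by the treating physician". No value is given for a participant who dies before the criteria are met.

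Statistical methods (2.8): "Data will be analyzed on an intention-to-treat basis", with between-group comparison by "Student *t* test or Mann–Whitney *U* rank sum test". No time-to-event method is named. Overall survival is a separate outcome (item 12).

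The Introduction gives a background figure for pleural infection: "mortality remains high at 8% in hospital and 20% at 3 months".

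**The concern.** For length of stay, short is read as good. A participant who dies on day 3 gets the value 3. One who goes home well on day 8 gets the value 8. Both named tests see only the number, so the death counts as the better result. If one arm has more early deaths, its stay is pulled down even when the drug does nothing to survivors' time in hospital.

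Time to clinical stability has a related gap. A participant who dies first has no time at all, and a t test or Mann–Whitney needs a value for everyone analysed under intention to treat.

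The stake is mainly in what follows the pilot. Its results are meant to set the endpoints and power calculations of later trials, and a stay distribution that mixes deaths with discharges would be carried into them.

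**Working it through.** **Inputs from the document.** N = 80, randomized 2:1 (Sample size). Significance at P < .05 (Statistical methods; two-sided assumed). In-hospital mortality of 8% (Introduction; background, not a design input).

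**Allocation.** 80 × 2/3 = 53.3 and 80 × 1/3 = 26.7, so about 53 versus 27. This agrees with the stated 50+ on dexamethasone. No power or effect size is given, so nothing else can be reproduced.

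**How often it arises.** At 8%: 80 × 0.08 = 6.4 deaths, and P(at least one) = 1 − 0.92^80 = 99.9%. At an assumed 2% to 5%: 1.6 to 4.0 deaths, and P(at least one) = 80% to 98%.

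**Mean shift.** Let the drug have no effect on survivors' stay, and let time of death have the same distribution in both arms. Then

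shift = (mortality on dexamethasone − mortality on placebo) × (mean time of death − mean stay of survivors).

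Assumptions not in the document: survivors' stay lognormal with median 8 days and log-SD 0.6; time of death lognormal with the same log-SD. Mean = median × exp(0.6²/2) = median × 1.197. Survivors' mean is 8 × 1.197 = 9.58 days. Mean time of death is 4.79, 9.58 or 14.37 days for medians of 4, 8 or 12 days.

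| Mortality, dexamethasone vs placebo | Median time of death | Shift in mean stay |
|---|---|---|
| 8% vs 8% | any | 0 |
| 16% vs 8% | 4 days | 0.08 × (4.79 − 9.58) = -0.38 day |
| 16% vs 8% | 8 days | 0.08 × 0 = 0 |
| 16% vs 8% | 12 days | 0.08 × (14.37 − 9.58) = +0.38 day |
| 4% vs 2% | 4 days | 0.02 × (4.79 − 9.58) = -0.10 day |
| 24% vs 8% | 4 days | 0.16 × (4.79 − 9.58) = -0.77 day |

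**Effect on the test.** Simulated Mann–Whitney, 53 versus 27, same model. The chance of a significant result favouring dexamethasone is nominally 2.5%.

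- 8% vs 8%: about 2.5%.
- 16% vs 8%: about 5% with deaths at a median of 4 days, about 2.6% at 8 days, 1% to 2% at 12 days.
- 4% vs 2%, deaths at 4 days: 3.0%.
- 24% vs 8%, deaths at 4 days: 9% to 10%.

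With deaths ranked worst, the chance at 16% vs 8% falls to about 0.5% whatever the timing. At 24% vs 8% it is about 0.1%.

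**A second set of assumptions.** Survivors' stay lognormal with median 6 days and log-SD 0.7; deaths uniform from 0.5 to 4, 12 or 24 days; 16% vs 8%. The probability that a dexamethasone stay exceeds a placebo stay (0.5 means no difference) is 0.470, 0.497 and 0.516 as defined, and 0.540 in all three cases with deaths ranked worst. As the protocol defines it, the direction depends on when deaths fall. With deaths ranked worst it does not.

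**Clinical stability.** If the discharge clause in item 1 is an alternative route to stability, every live discharge has a time. What remains without a time is a death (or a withdrawal or transfer) before stability.

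**The case against.** **Timing and size.** A late death scores as a long stay, and the table shows the shift vanishing and then reversing. The document does not give the timing of deaths. The 8% rate describes pleural infection. This trial takes all parapneumonic effusions, mostly simple ones, and excludes patients needing intensive care, so 8% is probably high. All of this stands. It limits the size of the bias but does not change how item 9 scores a death.

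**Masked harm.** A reader might infer that the plan could pass off a lethal drug as beneficial. The document does not support that. The 9% to 10% false-benefit figure needs 24% versus 8%, or about 53 × 0.24 = 12.7 deaths against 27 × 0.08 = 2.2. Survival is its own outcome, and all deaths go to the Data Safety Monitoring Committee.

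**Detail left to an analysis plan.** This is a fair answer for much of 2.8, but not for item 9, where the article itself states the rule that joins death to discharge. For time to stability it carries more weight, since there only a scoring rule is absent. It would also be wrong to say that the plan drops never-stable participants in breach of intention to treat; nothing in the text drops anyone.

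**Wider readings that fail.** One might extend the point to participants sent to intensive care, to antibiotic duration and to overall survival. A participant in intensive care can still reach stability later. Antibiotic duration has no death clause. Nothing says survival will be compared by a t test, and a log-rank test left unnamed is ordinary condensation in an article.

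**Conclusion.** The point holds for length of stay as defined. Item 9 and the named tests together score an in-hospital death like a live discharge on the same day, and an early death as a short stay. Bias between arms requires that mortality or the timing of death differ. It favours the arm with more deaths only when those deaths come earlier than typical discharges. Under the assumptions shown, the shift lies between about -0.4 and +0.4 day at 16% versus 8% and is about -0.1 day at 4% versus 2% with early deaths. It is zero when mortality and timing are equal.

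For time to clinical stability the point is narrower: deaths before stability have no value that the named tests could use.

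Severity is moderate to low. The trial is an exploratory pilot with no designated primary outcome, and survival is reported alongside. It is still worth correcting, because the pilot is meant to guide endpoint choice and sample size for later trials.

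**What to change.** In Outcomes (2.3) and Statistical methods (2.8), or in the analysis plan with an explicit override of item 9:

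- **Length of stay.** Either analyse time to discharge alive, with death as a competing event (cumulative incidence by arm), or keep the Mann–Whitney and rank every pre-discharge death worse than the longest observed stay.
- **Time to clinical stability.** Treat participants who die before stability as never stable. Give them the worst rank, or keep them in the risk set to a fixed day, such as Day 30, in a time-to-event analysis. State whether discharge home is an alternative route to stability.

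The cost is a change of wording, best made before unblinding. Items 9 and 12 already require the dates of discharge and death, so no new data are needed.

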### Sample size

2.4

In the absence of existing data, this pilot study aims to recruit 80 participants over 18 months. This will allow inclusion of the full range of parapneumonic effusions at various stages from simple parapneumonic stage (most common) to empyema (about 5–10% of all cases). The 2:1 randomization strategy will include 50+ participants into the dexamethasone arm to increase the power of detecting treatment related adverse events. The results of this pilot study will inform the power calculation of future studies and determine the most appropriate endpoints of future trials. Past evidence and data suggest that we will be able to estimate a range of outcome parameters with a high enough degree of accuracy with a sample size of 80 and allow some initial comparisons between treatment and placebo. The number of patients included over this timeframe will inform the feasibility and design of further studies.

